### Measurements

#### Overview

Table 1 gives an overview of all measurements. Participants are asked to fill out the questionnaires at baseline (T0); 3 months after the baseline measurement (T1); and 6 months after the baseline measurement (T2).

**Table 1 Tab1:** Overview of study parameters, measurement instruments and measurement points

Measure	Instrument	Filled out by Person with dementia	Informal caregiver
*Inclusion criterion*			
*(Very) Mild dementia*	CDR	T0	T0
*Exclusion criterion*			
*Trauma*	MINI Psychiatric Interview, module PTSD	T0	
*Primary outcome measure*			
*Neuropsychiatric symptoms of person with dementia*	NPI, total score		T0, T1, T2
*Secondary outcome measures*			
*Caregiver burden*	NPI, module Distress		T0, T1, T2
	EDIZ		T0, T1, T2
	TOPICS-MDS, modules Time investment and Burden		T0, T1, T2
*Quality of life of caregiver*	TOPICS-MDS, modules CarerQol and Quality of life (RAND-36 and variant of Cantril’s Self Anchoring Ladder)		T0, T1, T2
*Health of caregiver*	TOPICS-MDS, module Health (RAND-36)		T0, T1, T2
*Health-economic evaluation*			
*Care consumption*	TOPICS-MDS, module Use of care		T0, T1, T2
*Health-related quality of life of person with dementia*	TOPICS-MDS, module EQ5D + Cognitive	T0, T1, T2	
*Personal Information*			
*Socio-demographics*	TOPICS-MDS, module General data		T0
*Personal functioning of person with dementia*	TOPICS-MDS, modules Daily functioning (Katz-15) and Social functioning (RAND-36)	Daily functioning: T0, T1, T2	Daily functioning & Social functioning: T0, T1, T2
*Health of person with dementia*	TOPICS-MDS, modules Health and Multimorbidity	Health: T0, T1, T2	Multimorbidity: T0, T1, T2
*Psychological well-being of person with dementia*	TOPICS-MDS, module Psychological well-being	T0, T1, T2	
*Quality of life of person with dementia*	TOPICS-MDS, module Quality of life (RAND-36 and variant of Cantril’s Self Anchoring Ladder)	T0, T1, T2	
*Longer term outcome*			
*Nursing home admittance*	Addressed in month 18 with general practitioner		
*Process evaluation*			
*Other (reminiscence) activities*	Open question		T1, T2
*Use of OLSB*	Open questions		T1, T2

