##### Caregiver Burden

Caregiver burden is a secondary outcome measure. It is measured with a Dutch questionnaire (Ervaren Druk door Informele Zorg or EDIZ) [45]. This instrument has been used in informal caregivers with dementia and proved to be reliable and valid in this group. The informal caregiver rates the subjective burden on nine items with a five-point scale ranging from 1 = no! to 5 = yes!. The answers are dichotomized per item and then added up to a score between 0 and 9.

Caregiver burden is also measured with the distress scales of the NPI [41, 42]. The caregiver rates the distress for each of the twelve neuropsychiatric symptoms on a scale from 0 = none to 5 = severe. These twelve distress scores are summarized to a total score, ranging from 0 to 60. This sum score provides an indication of the emotional distress caused by all neuropsychiatric symptoms. Thirdly, the modules Time investment and Burden of the TOPICS-MDS are used to assess caregiver burden.

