#### Randomization check

Chi-square tests and t-tests will be used to check whether the randomization has succeeded in terms of personal information and functioning (TOPICS-MDS), neuropsychological complaints (NPI), caregiver burden (NPI and EDIZ), quality of life of the person with dementia (EQ5D + Cognitive), and quality of life of the caregiver (CarerQOL). When significant differences are found at baseline, we will assess whether these attenuate the outcomes later in time. If that is the case, we will control for these confounding variables in later analyses on the effects of the intervention.

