#### Effects

To analyze the effects on the primary outcome (total neuropsychiatric symptoms), repeated measures MANOVA will be used to assess the group differences across time. The condition (intervention vs. control) is the independent variable and the outcome measures across the three measurements are the repeated dependent variables. Simple contrasts will be used post-hoc to compare the post-intervention and follow-up measures with the pre-intervention measures. Effect sizes at post-intervention and follow-up will be calculated as Cohen’s d. Effect sizes between .56 and 1.2 are interpreted as large, between .33 and .55 as moderate, and below .33 as small [53].

We will also tentatively study the effects of the intervention on the four clusters of neuropsychiatric symptoms (hyperactivity, psychosis, affective symptoms, and apathy). As these measures are often not normally distributed, we will use a dichotomized outcome (clinically relevant symptoms or not, based on a FxS score of 4 and higher) [43]. We will carry out four logistic regression analyses with condition (intervention versus control) and presence of clinically relevant symptoms within the respective clusters at baseline as independent variables and presence of clinically relevant symptoms at follow-up as dependent variable. The odds-ratios will be used to provide estimates of the effect sizes in terms of Cohen’s d.

For the secondary outcome measures, three repeated measures MANOVA’s will be conducted, similar to the analysis for the primary outcome. The effect sizes will be given in Cohen’s d.

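### Three MANOVAs are planned for seven caregiver measures: a pooled burden test has no direction, and the text does not say that signed estimates will be given for each scale

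*Protocol article*

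**What the plan says.** Table 1 and the Secondary outcomes section of the protocol article list three caregiver domains measured by seven scales or modules:

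- Burden (four): NPI distress, EDIZ, and two modules listed as "TOPICS-MDS, modules Time investment and Burden". The Caregiver Burden section confirms the last two: "Thirdly, the modules Time investment and Burden of the TOPICS-MDS are used to assess caregiver burden".
- Quality of life (two): CarerQol and the TOPICS-MDS Quality of life module.
- Health (one): the TOPICS-MDS Health module.

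On analysis, the Effects section says "For the secondary outcome measures, three repeated measures MANOVA" analyses will be done, "similar to the analysis for the primary outcome", with effect sizes as Cohen's d. The primary analysis takes one score, the NPI total; in its model "the outcome measures across the three measurements are the repeated dependent variables". It is followed by contrasts against baseline: "Simple contrasts will be used post-hoc to compare the post-intervention and follow-up measures with the pre-intervention measures". The article does not say which caregiver measures enter which of the three MANOVAs, or whether the contrasts and effect sizes are per scale.

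**The concern.** Seven measures do not fit three analyses of the primary type, which handles a single score. If three is kept, several scales must share a test or some scales go without one.

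Secondary objective 1 concerns the effect on caregiver burden and quality of life, and the Discussion expects the intervention to help with both. That is a directional question. A multivariate test of several scales at once asks only whether the arms differ in some way. Its statistic is the same if every effect is reversed, and it can be large when scales contradict each other. A significant burden MANOVA would therefore not by itself show lower burden. If signed estimates per scale are not fixed in advance, the scales that explain the result can be chosen after the data are seen.

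**Working it through.** **1. The plan's own figure.** The Sample size calculation section gives f = 0.15, alpha = .05, power = .80, two groups, three measurements, r = .50. For the group-by-time interaction, λ = f²·N·m/(1−r) = 0.0225 × 74 × 3 / 0.5 = 9.99, with 2 and 144 df. Power is 0.806, so 74 reproduces; 74/0.70 = 105.7, hence 106. The article gives no power for the secondary analyses.

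**2. The count.** 4 burden + 2 quality of life + 1 health = 7 measures, against 3 MANOVAs. This counts instruments and modules. Splitting off the CarerQol happiness scale, the RAND-36 items or the Cantril ladder would raise it.

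**3. Degrees of freedom with one MANOVA per domain.** Three time points give two contrasts against baseline (T1−T0 and T2−T0). Group by time then has scales × 2 df: burden 4 × 2 = 8, quality of life 2 × 2 = 4, health 1 × 2 = 2.

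**4. Direction.** Hotelling's T² is proportional to δ′Σ⁻¹δ, which does not change when δ becomes −δ. Simplified illustration: one contrast per scale, four scales, N = 74, d = 0.3, between-scale correlation .3, and quantity (N/4)·δ′Σ⁻¹δ:

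- all four improve: 3.5
- all four worsen: 3.5
- two improve and two worsen: 9.5

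**5. Power of the pooled burden test.** N = 74 and r = .50 are from the article. The effect d = 0.40 at both T1 and T2, and the between-scale correlation ρ, are assumptions; the article gives neither.

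One scale: with r = .50 the two change scores each have variance 1 and covariance 0.5, so δ′Σ⁻¹δ = 1.333·d². Noncentrality is (74/4) × 1.333 × 0.16 = 3.95, on 2 and 71 df, and power is 40%.

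Four scales: 3.95 is multiplied by 4/(1+3ρ) if all move together, by (1+2ρ)/((1−ρ)(1+3ρ)) if only one moves, and by 4/(1−ρ) if two improve and two worsen, on 8 and 65 df.

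| ρ | all four together | one only | two up, two down |
|---|---|---|---|
| .3 | ×2.11, 44% | ×1.20, 25% | ×5.71, 92% |
| .5 | ×1.60, 33% | ×1.60, 33% | ×8.00, 98% |
| .7 | ×1.29, 27% | ×2.58, 54% | ×13.3, over 99% |

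The first column is the same whether all four improve or all four worsen. Against 40% for one scale, the pooled test is better at ρ = .3 and worse at .5 and .7.

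**6. What a baseline-adjusted analysis per scale offers.** At T2, with N = 74, d = 0.40 and r = .50, the change score has variance 2(1−r) = 1, so the noncentrality is 0.40 × √(74/4) = 1.72 and power about 40%. Adjusting for baseline leaves variance 1−r² = 0.75, so the noncentrality is 1.72/√0.75 = 1.99 and power 50%.

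**7. Multiplicity.** Three independent tests at .05 give 1−0.95³ = 0.143; seven give 1−0.95⁷ = 0.302.

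**The case against.** The strongest reply is that nothing is broken. Table 1 has exactly three secondary domains, the text uses the same three headings, and one multivariate test per domain is a recognised way to limit the number of tests. That stands: three MANOVAs can cover the outcomes, and a reader who infers that they cannot goes too far.

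Second, the omnibus p-value is not the whole analysis. Modelling it on the primary analysis brings in the contrasts against baseline, and Cohen's d is promised. Both are signed, and d has to be computed on some scale. This also stands, but only in part, because the article never says that they will be given for each scale.

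Third, a reader might infer that only NPI distress, EDIZ and CarerQol will be tested, leaving four measures without a comparison between arms. The support is that the Descriptive statistics and Randomization check sections name just these, for example "quality of life of the caregiver (CarerQOL"). Those lists serve description and a baseline check. The Effects sentence refers to the secondary outcome measures without restriction, and Table 1 puts all seven under that heading. The documents do not support this reading as the plan.

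Fourth, it is tempting to say that pooling loses power, or that the pooled test is always weakest against a consistent improvement. Neither holds in general. At ρ = .3 the pooled test beats a single scale (44% against 40%), and there the hardest pattern to detect is a change on one scale (25%). The two-up, two-down pattern shows what the test responds to; nothing in the article suggests that it will occur.

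Finally, an article may leave the assignment of scales to a fuller document. That is fair for the mapping alone. But the article itself fixes the number and form of the tests, and these do not match its list of measures unless scales are pooled.

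**Conclusion.** The point holds in a limited form. The article fixes three MANOVAs for seven caregiver measures. On the most natural reading the burden test pools up to four scales on 8 df; it has no direction and no single Cohen's d, and cannot by itself answer secondary objective 1. Per-scale contrasts and effect sizes would answer it, but are not stated to be per scale.

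The count of seven and the 8 df follow from the article, counting instruments and modules. The power figures rest on an assumed d and assumed between-scale correlations, and support no claim of a general power loss. The case for separate adjusted analyses is that they are signed and easy to interpret and, under the stated assumptions, raise power on a single scale at T2 from about 40% for a change score to 50%. This is an improvement that should be made, not a threat to the trial's main conclusion.

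**What to change.** Replace the sentence on secondary outcomes. Give each of the seven caregiver scales or modules its own comparison between arms at T1 and T2, adjusted for its baseline value, and report a signed mean difference with 95% CI and Cohen's d. Report all seven. Name in advance one lead scale for burden and one for caregiver quality of life, on which objective 1 will be judged, and label the others supportive. EDIZ and CarerQol are candidates, since the article already singles them out, but they are not the only valid choice.

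If the sponsor keeps the MANOVAs, the minimum is to state which scales enter each one and that contrasts and Cohen's d will be given for every scale.

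The cost is wording only: baseline is already collected for every scale. The downside is that more estimates are reported, so the supportive ones need a statement that they are not adjusted for multiplicity, and the lead scales must be chosen before the data are seen.

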##### Health-economic evaluation

The preliminary health-economic evaluation will be done from a healthcare perspective. It is expected that the costs of the intervention will be earned back through the reduction in care consumption. The health-economic evaluation will be carried out according to the intention-to-treat principle. Bootstrapping techniques with 95% confidence intervals will be used to compare the differences in costs between the intervention and the control condition. The incremental cost-utility ratios (ICERs) will be computed. These indicate the extra costs per QALY (measured with the EQ5D + C) gained. A sensitivity analysis will be conducted to assess the robustness of the results by assessing the mean costs (plus or minus a standard deviation) for the most important expenses.

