#### Sample size calculation

Based on systematic reviews [15, 17, 18], a small significant effect is expected for the primary outcome at follow-up. Hence, 74 participants are needed (GPower: f = 0.15; alpha = .05; power = .80; repeated measures anova with 2 groups and 3 measurement points; *r* = .50 between measurements). Given the vulnerability of the participants and a high mortality rate, we expect a drop-out of 30% [15, 17, 18]. Hence, 106 participants need to be included, 53 per condition.

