#### Health-economic evaluation

*Care consumption* of the person with dementia will be used in the preliminary health-economic evaluation that provides a time window of 6 months, parallel to the RCT. Care consumption is measured in the TOPICS-MDS [44]. Care consumption includes medical costs (e.g., visits of general practitioner, specialist physicians, and hospital care) as well as indirect non-medical costs (e.g., home care, travel costs). Costs will be evaluated, based on the manual of Tan et al. (2012) [49].

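### The economic evaluation declares a healthcare perspective but counts travel and other indirect non-medical costs; its ±1 SD sensitivity range is also a poor plausible range for a mean cost

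*Protocol article*

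**What the plan says.** Two sections of the protocol article carry the heading Health-economic evaluation.

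- Under Statistical analyses: "The preliminary health-economic evaluation will be done from a healthcare perspective". The ratio is then defined: "These indicate the extra costs per QALY (measured with the EQ5D + C) gained".
- Under Measurements, the patient's recorded use of care is the cost input, which "will be used in the preliminary health-economic evaluation that provides a time window of 6 months, parallel to the RCT". Its content is medical costs "as well as indirect non-medical costs (e.g., home care, travel costs").

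Uncertainty is handled in two steps, both under Statistical analyses. For sampling error: "Bootstrapping techniques with 95% confidence intervals will be used to compare the differences in costs between the intervention and the control condition". For robustness, a sensitivity analysis is planned "by assessing the mean costs (plus or minus a standard deviation) for the most important expenses". The text does not say which standard deviation is meant, or how the change is applied to the two arms.

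**The concern.** The perspective decides which costs enter the numerator of the cost-utility ratio. A healthcare perspective normally leaves out non-medical items such as travel, yet the measurement section puts them into the cost input. An analyst who follows both sections produces a ratio labelled with one perspective and computed on the costs of another. An analyst who notices the clash must choose a cost set, possibly after seeing the data. The plan expects intervention costs to be recovered through lower care consumption, so the choice of cost set bears directly on the question asked.

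The sensitivity range raises a lesser question. A standard deviation between patients describes how far individuals differ, not how far the mean cost could plausibly lie from its estimate. Used as a range for a mean, it may be much too wide and may include impossible values.

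**Working it through.** **1. Cost scope.** Setting the two sections side by side:

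- Declared perspective (Statistical analyses): healthcare.
- Cost input (Measurements): medical costs plus indirect non-medical costs, with home care and travel as the examples.
- Text restricting the numerator to healthcare costs: none.
- Text defining the perspective so as to include travel: none.

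Write ΔH for the between-arm difference in mean healthcare cost, ΔT for the difference in travel and similar costs, and ΔQ for the difference in QALYs. The healthcare ratio is ΔH/ΔQ. The ratio from the listed cost set is (ΔH + ΔT)/ΔQ. They differ by ΔT/ΔQ. The article gives neither ΔT nor ΔQ, so the size and direction of this term cannot be derived. Home care is less clear than travel: formal home care can be counted as care, and its place under the non-medical label may be only a matter of naming.

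**2. Sample size behind the ±SD check.** The section Sample size calculation gives "GPower: f = 0.15; alpha = .05; power = .80; repeated measures anova with 2 groups and 3 measurement points", with r = .50.

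- λ = f²·N·m/(1 − r) = 0.0225 × 74 × 3 / 0.5 = 9.99, with 2 and (74 − 2) × 2 = 144 degrees of freedom. Power is 0.806, so the stated 74 is reproduced for the group-by-time interaction.
- Drop-out: 74/(1 − 0.30) = 105.7, rounded up to 106, or 53 per arm. This also agrees.

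**3. ±1 SD against the uncertainty in a mean.** Assume the SD is between patients and equal in the two arms. Then SE(arm mean) = SD/√n, SE(difference) = SD·√(2/n), and the 95% half-width is 1.96·SE.

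| n per arm | Quantity | SE | 95% half-width | 1 SD ÷ SE | 1 SD ÷ half-width |
|---|---|---|---|---|---|
| 53 | arm mean | 0.137 SD | 0.27 SD | 7.3 | 3.7 |
| 53 | difference | 0.194 SD | 0.38 SD | 5.1 | 2.6 |
| 37 | arm mean | 0.164 SD | 0.32 SD | 6.1 | 3.1 |
| 37 | difference | 0.232 SD | 0.46 SD | 4.3 | 2.2 |

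The rows for 53 are all randomized participants, which is the intention-to-treat set. The rows for 37 are the completers expected after 30% drop-out.

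**4. The lower limit.** The article gives no coefficient of variation (CV = SD/mean), so a range is assumed. Figures are multiples of the mean; the last column is 1 ± 1.96·CV/√53.

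| CV (assumed) | mean ± 1 SD | 95% interval of the mean, n = 53 |
|---|---|---|
| 0.5 | 0.5 to 1.5 | 0.87 to 1.13 |
| 1 | 0 to 2 | 0.73 to 1.27 |
| 1.5 | −0.5 to 2.5 | 0.60 to 1.40 |
| 2 | −1 to 3 | 0.46 to 1.54 |

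From CV = 1 upwards the lower scenario is a zero or negative mean cost. The confidence interval stays above zero throughout this range.

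**5. What the range does to the cost difference.** This depends on an unstated rule, with arm means m1 and m0.

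- The same SD added or subtracted in both arms: (m1 − SD) − (m0 − SD) = m1 − m0, so nothing changes.
- Both arms scaled in proportion: the item's share of the difference is multiplied by 1 ± CV. At CV = 1 that is 0 to 2, with no change of sign.
- One arm shifted alone: the difference moves by 1 SD, against a 95% half-width of 0.38 SD at 53 per arm.

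**The case against.** The strongest defence of the cost scope is that the mismatch is mostly labelling. Home care can be read as care, which leaves travel as the only named item in conflict, and the text does not say who pays for it. That stands as a limit on the point but does not remove it: the measurement section still sends travel into an evaluation declared as healthcare only.

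On the ±SD range, the defence is that this is a deterministic stress test of selected expenses, and that bootstrap intervals already cover sampling error in the cost difference. This largely stands. The range is not offered as a confidence interval, so its width is not in itself an error. What remains is that it is a poor choice of plausible values for a mean, with neither the SD nor its application to the arms defined.

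A reader might infer more than the document supports:

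- That the cost-utility ratio is itself wrong. Its definition, extra cost per QALY gained, is standard; only its cost scope is inconsistent.
- That the sensitivity analysis would find almost any result not robust. Step 5 shows that this depends on a rule the text does not give, and under a common shift the result does not move at all.
- That caregiver time is wrongly left out. Under a healthcare perspective it belongs outside the cost set, and the plan measures it as caregiver burden.
- That the plan expects a negative ratio. It expects intervention costs to be recovered, which is compatible with breaking even. Net-benefit reporting is commonly left to the full plan.

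**Conclusion.** The point holds as a contradiction in stated text: the declared healthcare perspective and the listed cost components do not agree, and nothing in the article settles which governs. Travel is the firm part of the conflict; home care is doubtful. The ratio moves by ΔT/ΔQ, whose size is unknown because no costs are given.

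The ±SD point is secondary and conditional. If the SD is between patients, the range is about 3.7 times the 95% half-width of an arm mean at 53 per arm (3.1 at 37), and 2.6 times that of the between-arm difference (2.2 at 37). The zero-or-negative lower limit further assumes a CV of at least 1. This makes the range poorly chosen and underspecified, but it does not invalidate the robustness check.

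The evaluation is one of four secondary objectives and is described as preliminary. The primary analysis of neuropsychiatric symptoms is not affected. The correction is still worth making, because it settles before analysis which costs enter a reported result.

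**What to change.** 1. Reconcile the two sections with one cost list. Either make the base case healthcare costs only (medical care, formal home care and the cost of delivering the intervention) and move travel to a separately labelled wider-perspective analysis, or keep the present list and rename the perspective to match it. State under which heading home care falls.
2. Replace ±1 SD with the bootstrap 95% limits of the mean for each main expense, or with stated percentage changes in unit prices. Say whether the change is made in both arms together, in proportion, or in one arm at a time.

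The cost is a few sentences in the plan and a little extra computation. No new participant data are needed, provided travel can be separated from the other items in the care-use data (an assumption, since the article does not list the items).

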##### Health-related quality of life of person with dementia

To measure health-related quality of life, the EQ5D + Cognitive will be used [50], a short questionnaire with 6 items that is also part of the TOPICS-MDS. This study will use Dutch tariffs to calculate the quality adjusted life years (QALYs) to obtain a utility score.

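### The economic evaluation prespecifies no adjustment for T0 utility or T0 care use, and the only covariate rule in the protocol depends on a significant baseline test and does not list care consumption

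*Protocol article*

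**What the plan says.** Under Statistical analyses, Health-economic evaluation, the protocol article states the method for costs: "Bootstrapping techniques with 95% confidence intervals will be used to compare the differences in costs between the intervention and the control condition". It then plans incremental cost-utility ratios and explains them: "These indicate the extra costs per QALY (measured with the EQ5D + C) gained". No baseline covariate is named for costs or for QALYs. The only sensitivity analysis there varies mean costs.

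Under Measurements, Table 1 lists "TOPICS-MDS, module EQ5D + Cognitive" for the person with dementia and "TOPICS-MDS, module Use of care" for the informal caregiver, each at T0, T1 and T2. The economic analysis is described as a "preliminary health-economic evaluation that provides a time window of 6 months, parallel to the RCT". On utilities, the article says: "This study will use Dutch tariffs to calculate the quality adjusted life years (QALYs) to obtain a utility score". It does not say how the three utilities are combined into a QALY.

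The one covariate rule is under Randomization check. Baseline tests are run on a list of variables that includes EQ5D + Cognitive and does not name care consumption. The rule continues: "When significant differences are found at baseline, we will assess whether these attenuate the outcomes later in time". Adjustment follows only if they do.

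**The concern.** T0 utility and T0 care use are likely to predict the same quantities at T1 and T2. If the QALY is built by linear interpolation over the 6 months, T0 utility is also one of its components. A baseline difference left by chance then enters the QALY difference twice: directly through the T0 weight, and indirectly through its correlation with T1 and T2. The QALY difference is the denominator of the ICER.

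The gated rule acts only on large imbalances, and it does not list care consumption. Elsewhere under Effects the baseline value is always used: the repeated measures analysis includes T0, and the four logistic regressions for symptom clusters include baseline symptom status whatever the baseline tests show. Among the outcomes measured at all three visits, the economic ones are the exception.

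At stake is the precision of the result for secondary objective 2 and how far it depends on chance imbalance. A sensitivity analysis that varies only mean costs would not reveal this.

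**Working it through.** **The protocol's own figure.** The economic evaluation has none. The sample size section gives f = 0.15, alpha .05, power .80, two groups, three measurements and r = .50. For the group-by-time interaction, λ = f²·N·m/(1 − r) = 0.0225 × 74 × 3 / 0.5 = 9.99 on 2 and 144 df, which gives power 0.806 at N = 74 (0.795 at N = 72). Then 74 / 0.70 = 105.7, so 106, or 53 per arm. The stated figures reproduce. They concern the primary outcome (NPI), so using r = .50 for utility or cost is an assumption.

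**Further assumptions, none given in the document.** Equal variances at the three visits (utility SD = 1), a common correlation r, complete data, and QALY = 0.125·U0 + 0.25·U1 + 0.125·U2 (trapezoid over 6 months).

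**Variance explained by T0 utility.**
- Var(QALY) = 0.09375 + 0.15625·r, which is 0.1719 at r = .5.
- Cov(QALY, U0) = 0.125 + 0.375·r, which is 0.3125 at r = .5.
- R² = Cov²/Var = (1 + 3r)²/(6 + 10r). At r = .5 this is 6.25/11 = 0.568.
- SE ratio, adjusted to unadjusted: √(1 − 0.568) = 0.657, so the SE is 34% smaller.

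If T0 is left out of the QALY and T1 and T2 have equal weight, R² = 2r²/(1 + r). The same formula applies to follow-up cost taken as T1 + T2 and adjusted for T0 cost.

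| r | QALY including T0 | QALY without T0, or cost T1 + T2 |
|---|---|---|
| 0.3 | 0.40 | 0.14 |
| 0.5 | 0.57 | 0.33 |
| 0.7 | 0.74 | 0.58 |

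If the correlation instead decays with time (0.5 between adjacent visits), R² for the QALY including T0 is 0.48.

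**What the gated rule recovers.** In 20,000 simulated trials at 53 per arm and r = .5, the variance of the QALY difference was 0.00655 unadjusted, 0.00552 when adjusting only after a significant baseline t-test, and 0.00281 when always adjusting. The reductions are 16% and 57%. A hand check agrees. The share of a standard normal's variance lying beyond ±1.96 is 0.05 + 2 × 1.96 × 0.0584 = 0.279, and 0.279 × 0.568 = 0.16. The simulation treats the rule's second condition as always met, so 16% is if anything generous.

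**How far an untriggered imbalance carries (r = .5, 53 per arm).**
- SE of the baseline difference: √(2/53) = 0.194 SD.
- Largest non-significant difference: 1.983 × 0.194 = 0.385 SD.
- SE of the unadjusted QALY difference: √(0.1719 × 2/53) = 0.0805 SD-years.
- Expected shift from a one-SE imbalance: 0.3125 × 0.194 = 0.061 SD-years, or 0.75 SE.
- Expected shift from an imbalance just short of significance: 0.3125 × 0.385 = 0.120 SD-years, or 1.5 SE. For an assumed utility SD of 0.20 to 0.30 that is 0.024 to 0.036 QALY.

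**The case against.** The strongest reply is that the economic section never says its comparison is unadjusted. It is a condensed paragraph in a journal article, and a QALY formula and bootstrap covariates are commonly left to a fuller document. That stands as far as it goes: silence in that section is no fault by itself. But the article does state a covariate rule for analyses of intervention effects, and the rule is the weak part. It waits for significance, and its list omits care consumption.

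Second, a reader might infer that the economic result would be biased, or that there is no protection against imbalance in utility. Neither follows. Under randomisation the unadjusted difference is unbiased and its interval already allows for chance imbalance. A large imbalance in EQ5D + Cognitive can also trigger adjustment.

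Third, a reader might infer that an ordinary non-significant imbalance could reverse the sign of the QALY difference. The arithmetic does not show this. For an assumed utility effect of 0.33 SD at T1 and T2, the true QALY difference is 0.375 × 0.33 = 0.124 SD-years. An imbalance just short of significance shifts it by 0.120/0.124 = 97%, which is not a reversal, and an imbalance that large is uncommon. A one-SE imbalance shifts it by 49%.

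Fourth, the article plans no hypothesis test on QALYs, so statements about power would concern an analysis it does not contain. It also calls the evaluation preliminary. Both points stand and limit the weight of this comment.

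**Conclusion.** The point holds as one of efficiency and robustness, not validity. The economic section names no baseline adjustment. The rule that could supply it is gated on significance, recovers little, and does not list care consumption, although both baseline values are collected.

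Under the stated assumptions, planned adjustment for T0 utility removes about 40% to 74% of the variance of the QALY difference for r from 0.3 to 0.7, and 57% at 0.5. If T0 is left out of the QALY, the figure at 0.5 is about 33%. The gated rule gives about 16% at 0.5. The size depends on correlations and an area rule that the article does not give; for any positive correlation the direction does not.

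It would be tempting to say that the unadjusted analysis loses more than half its precision. That is true only if precision means inverse variance, T0 is in the QALY and r exceeds about 0.42. On the standard-error scale the loss at r = .5 is 34%, and it passes half only above about 0.71. The change is worth making because it costs almost nothing, but it is not the correction of an error.

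**What to change.** In the Health-economic evaluation paragraph of the analysis section, prespecify that:

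- each bootstrap resample draws a participant's costs and utilities together;
- within each resample, the incremental QALY comes from a regression of 6-month QALY on arm and T0 EQ5D + Cognitive utility;
- within each resample, the incremental cost comes from a regression of follow-up cost on arm and T0 care cost;
- the ICER and its interval are formed from these two adjusted increments, whatever the Randomization check shows;
- the unadjusted ICER is reported as a sensitivity result.

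The cost is a few sentences of analysis text and two covariates in the bootstrap code. No new data, visits or participants are needed. The drawback is that a linear cost regression is somewhat sensitive to very high baseline costs. The bootstrap distribution and the unadjusted sensitivity result would show whether that matters.
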